#### 2.4.4. Biochemical Measurements

To explore whether biological markers in body specimen are associated with lifestyle change and may be used as a guide star, we draw blood by vena puncture (mos. 0, 12, 24) and by finger-prick (mos. 0, 6, 12, 24), and ask the participant to collect feces (mos. 0, 12, 24).

##### Vena Puncture

Biochemical measurements such as anti-oxidants, fat soluble vitamins, minerals, fatty acids, lipids, complement factors, and inflammatory markers are sampled from serum, EDTA plasma, and whole blood obtained by vena puncture. All samples are prepared for each required analysis according to standard methods. Aliquots are stored (−80 °C) for later analysis.

##### Finger-Prick

To assess whether results from finger prick measurements performed at home may also be used as biological markers of adherence, we ask participants to collect dried whole blood spots (DBS) on a 903 protein saver card from Whatman (mo. 6 at home, mos. 0, 12, 24 at RC) [46,47]. Finger-prick biomarkers assays include anti-oxidants, fat soluble vitamins, minerals, and fatty acids.

##### Collecting Feces

To measure diversity and composition (i.e., alpha and beta diversity and single taxa) of the fecal microbiome over time, we ask participants to collect a sample of their feces at home at three time points: mos. 0, 12, and 24. Participants receive a feces collection kit with all necessary materials. The sample is collected using a preservative and stored at –80 °C upon arrival at the research center for later analysis. Medication use (such as antibiotics) is registered as well (yes/no; if yes, which).

#### 2.4.5. Lifestyle Factors

##### Smoking

Smoking habits are assessed by questionnaire at mos. 0, 3, 6, 9, 12, and 24. Questions include smoking of cigarettes, cigars, tobacco pipe: yes, currently/yes, but quit/no never/; year of smoking cessation; number of cigarettes/cigars/pipe per day; number of years of smoking.

##### Dietary Assessment and Supplement Use

A 389-item food frequency questionnaire (389-FFQ) developed for Dutch adults [48,49] is used to measure dietary behavior at mos. 0, 12, and 24. The 389-FFQ records frequency of each intake as times per day, per week, or per month. The portion sizes are in grams per day (g/day). Nutrient intake data are calculated using the Dutch Food Composition Tables [50], in close collaboration with the Department of Human Nutrition, Wageningen University, the Netherlands. The 389-FFQ was validated against other dietary assessment methods, and adequate ranking of participants according to food and nutrient intake was demonstrated [48,49,51,52]. Oral supplement use (yes or no) is measured using self-reported questionnaires at different time points.

Adherence to Mediterranean diet is scored in two ways: (1) analysis of data from the 389-FFQ; (2) analysis of data from the validated 14-point MeDiet screening instrument [53,54] at mos. 0, 3, 6, 9, 12, and 24. The 14-point MeDiet screening instrument is a modified version of the original standardized Mediterranean Diet Score (MDS) [23,24]. We added two additional questions to this instrument in our version (Table 1).

The 16-point MeDiet is used as part of the lifestyle form that is available for groups B and C. In the lifestyle form, outcomes of 13 out of the 16 questions, as indicated in Table 1, are used.

##### Physical Activity

Physical exercise is assessed using the validated ‘Women’s Health Initiative (WHI) Physical Activity Questionnaire’ [55] at mos. 0, 12, and 24. The WHI Physical Activity Questionnaire is a common instrument and has previously been used in several AMD studies [19]. The questionnaire contains questions on walking, cycling, gardening, various sports, and housekeeping, according to time spent in light, moderate, and vigorous activity.

##### Feasibility and Acceptability

To assess feasibility and acceptability, we ask participants about their own experience with AMD, their experience with the recommendations, and depending on the intervention group, we ask about their experience with the personalized risk score and additional coaching (mos. 3, 6, 9, 12, and 24) by a short questionnaire.

##### Assessment of Change in Habitual Behavior

All coaching sessions (Group C) are recorded by video and registered in the AMD-Life database. Reporting includes motivation, goal-setting for change, self-confidence according to the AMD-Life coaching model (which aims to reflect an upwards spiral), and learning from potential relapses (Figure 2). In order to start the coaching process, we ask the participants at baseline to fill out a short questionnaire regarding (1) receiving information; (2) motivation, perseverance, and discipline; and (3) acceptance that unbeneficial but often enjoyable habit patterns need to change. Participants rank their motivation, perseverance, and discipline on a visual analogue scale (VAS) from 0 to 10 (with 0 representing no/lowest, 5 moderate, and 10 highest motivation, perseverance, and/or discipline). Subsequently, individual lifestyle goal(s) on one (or more) of the four lifestyle components (smoking, food pattern, weight, and/or physical activity) are defined. The following steps determine ambivalence/assessment status: the stages of change model (the transtheoretical Model of Change) [39,41]; and the ‘DARN-CAT’ motivational interviewing model (increasing/recognizing of ‘change talk’ using the six signs in the individual’s language) [40,41]. The contents of the coaching depend on the stage and/or need of the participant and lifestyle assessments. Documents with assignments and tables (e.g., specific foods and levels/concentrations of beneficial AMD-nutrients) are provided to enhance awareness and stimulate habitual change during these individual coaching sessions.

To measure, score, and visualize progression or relapse, and to enhance adherence during the coaching sessions, we developed a 13-point easy-to-use lifestyle scoring form (Figure S1) and a visualization form (Figure S2) for follow up. Both forms include the total GRS (Figure S1 page 2) and lifestyle information. Lifestyle risk estimates are based on validated studies (i.e., smoking, BMI, MeDiet (13 items), physical activity). Each healthy outcome receives a point. The total score can range from 0 to 13, in which high scores represent an AMD-healthy lifestyle (Figures S1 and S2).

The lifestyle score form is used at baseline for group B and C, and at each additional time point (mos. 0, 3, 6, 9, 12, and 24) for Group C. At the second (mo. 12) and third (mo. 24) visit at our research center, all participants receive the complete lifestyle score form and visualization thereof at mos. 0, 12, and 24, respectively. For a more detailed description, see the Supplementary Materials.

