## 2. Materials and Methods

### 2.1. Study Design and Population

AMD-Life is a 2-year lifestyle intervention trial. The first year is a self-contained open-label randomized clinical trial with 3 intervention arms. The second year aims to investigate the sustainability of improved lifestyle without active intervention. Patients visit the research center 3 times: at baseline, month 12, and month 24. Ethical approval was obtained from the Medical Ethical Committee at Erasmus MC (MEC-2018-063). AMD-Life is registered at ClinicalTrials.gov (registration identifier: NCT05667441).

This study is designed as an inception phase study. We set up the main elements, test our assumptions and feasibility, check procedures, and focus on adherence, reporting participant and physician experience for the three different strategies tested, specifically targeting long-term behavior change.

Sample size calculation indicated that 50 eligible subjects per group would be sufficient to detect an effect size of 0.25 for adherence to lifestyle recommendations after the 12-month intervention (alpha: 0.05, power: (1-beta err prob.): 0.8897, calculated by G*Power).

Recruitment for the study started 2 August 2021 and is expected to end 1 July 2023. Participants are made aware of the study by their attending physician at outpatient clinics (OPC) of Erasmus MC Rotterdam, the Rotterdam Eye Hospital, Radboudumc, in Nijmegen, and other hospitals in the Netherlands. Interested candidates can apply online through the website: www.maculadegeneratie.nl (accessed on January 2023) with the apply button for participation, or by email or telephone.

Inclusion criteria: age between 55 years and 85 years, a diagnosis of intermediate AMD or unilateral late AMD, as determined by multimodal imaging and approved by the EyeNED Reading Center.

Exclusion criteria: participation in other intervention studies for AMD; living in retirement homes (because of difficulty in implementation of diet); dementia; macular pathology other than AMD; liver and kidney insufficiency; persons who are illiterate and have no independent trusted person with them to explain the informed consent form.

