Prior to the study, all potential participants are informed and asked to provide written consent. Subsequently, participants are invited to visit the research center. Eligible participants are randomly assigned using a block-wise randomization procedure (in a 1:1:1 ratio) to one of three study arms. The assignment is by means of a computer-generated table with a random number sequence. This table gives a random order of allocation to the ‘Treatment Group’. The order is by date and time of the first study visit and stratified by gender and age categories (55–64, 65–74, 75–85). The first 125 participants are randomized per block (sets) of 6, and the remaining 25 per sets of 3. The researchers are blinded for randomization.

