### 3.1. Primary Study Outcome

Improvement of the overall lifestyle score was measured by the 13-point form (see previous paragraph and Figure S1: Lifestyle scoring form), which is based on the questionnaires inquiring about smoking habits, BMI, MeDiet, and physical activity taken at baseline and 12 months (see previous paragraph data collection and measurement).

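### The lifestyle form that scores the primary outcome is also feedback and coaching material in groups B and C, so part of any arm difference may be differential self-report

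*Protocol article*

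**What the plan says.** - **Primary outcome** (section 3.1): "Improvement of the overall lifestyle score was measured by the 13-point form". The score draws on questionnaires about smoking, BMI, MeDiet and physical activity at baseline and 12 months.
- **The form as intervention** (section 2.4.5, Assessment of Change in Habitual Behavior): "To measure, score, and visualize progression or relapse, and to enhance adherence during the coaching sessions, we developed a 13-point easy-to-use lifestyle scoring form". On timing, the same section says: "The lifestyle score form is used at baseline for group B and C, and at each additional time point"; the later time points apply to group C. Under Dietary Assessment and Supplement Use: "The 16-point MeDiet is used as part of the lifestyle form that is available for groups B and C". Section 2.2.2 has group B receive personal grades that show where they can improve.
- **Group A** (sections 2.2.1 and 2.2.3): standard recommendations in person and by letter, with insight into its own lifestyle changes at month 12.
- **Masking** (sections 2.1 and 4): the first year is open label. The blinding described concerns the randomization.
- **A second diet measure** (Dietary Assessment and Supplement Use): "Adherence to Mediterranean diet is scored in two ways", one from the 389-item food frequency questionnaire (FFQ) and one from the short MeDiet screener. The form uses the screener.
- **Limitations** (section 4): self-report is named for physical activity only.

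**The concern.** When an outcome instrument is also teaching material, a participant's answers can move without the behaviour moving. Here the amount of contact with the scoring differs by arm, and more contact goes with more intervention. If seeing one's grade or discussing it with a coach makes people answer more favourably, the distortion points the same way as the hoped-for effect. Participants supply the answers and know their arm, so blinding the researchers to the randomization does not help.

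What is at stake is the claim. Section 4 expects the trial, once validated, to show that lifestyle change is achievable in these patients. A higher form score supports that only if it reflects behaviour. Section 3 ties neither the FFQ nor the biomarkers to the reading of the primary result.

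**Working it through.** **1. Contact with the scoring, by arm**

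| | A | B | C |
|---|---|---|---|
| Answers the underlying questionnaires (Figure 3 legend) | yes | yes | yes |
| Receives the standard recommendations (section 2.2) | yes | yes | yes |
| Own grade on the form before month 12 | no | month 0 | months 0, 3, 6, 9 |
| Form used in coaching | no | no | yes |

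The arms differ in graded feedback, not in the questions asked.

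**2. Inputs.** Section 2.1 says that "50 eligible subjects per group would be sufficient to detect an effect size of 0.25 for adherence to lifestyle recommendations after the 12-month intervention", with "alpha: 0.05, power: (1-beta err prob.): 0.8897, calculated by G*Power". Allocation is made "using a block-wise randomization procedure (in a 1:1:1 ratio) to one of three study arms". So N = 150 in k = 3 arms of 50. I read 0.25 as Cohen's f, the SD of the arm means divided by the within-arm SD. The article gives no SD for the score.

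**3. The plan's own power figure**
- One-way ANOVA: λ = f²N = 0.0625 × 150 = 9.375 on 2 and 147 df. Power is 0.780, which does not match.
- Repeated-measures ANOVA, between-group effect, assuming m = 2 measurements with correlation ρ = 0.5: λ = f²Nm/[1 + (m − 1)ρ] = 0.0625 × 150 × 2 / 1.5 = 12.5. Power is 0.8898, against the stated 0.8897.

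The stated figure is therefore reproducible, though m and ρ are my assumptions and the article does not name the test. Below I apply f to the 12-month comparison, as section 2.1 words it.

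**4. f = 0.25 as a difference d between the extreme arms**
- One arm apart from the other two: f = d√2/3 = 0.471d, so d = 0.25/0.471 = 0.53 SD.
- Equally spaced arms: f = d/√6 = 0.408d, so d = 0.25/0.408 = 0.61 SD.

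**5. What a pure reporting shift would do.** Suppose no behaviour changes and group C over-reports by a fixed amount relative to A. The probability of a significant result with 50 per arm and two-sided alpha 0.05 is:

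| Shift in C | Three-arm test, B shifts as much as C | Three-arm test, B shifts half as much | C vs A alone |
|---|---|---|---|
| 0.25 SD | 0.23 | 0.18 | 0.24 |
| 0.50 SD | 0.73 | 0.59 | about 0.70 |

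These are simple ANOVA and two-group calculations, not the planned mixed model. They show sensitivity to an assumed shift and do not estimate its size.

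**6. Why this stays in SD units.** Table 1 ticks 13 MeDiet items for the form. The form also covers smoking, BMI and physical activity, making 13 + 3 = 16 components, yet the total runs from 0 to 13. The weight of one diet item therefore cannot be read from the text. Eight of the 13 ticked items also have a half-point category.

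**The case against.** Much can be said for the plan.

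- **The score appears to come from common data.** Section 3.1 bases it on questionnaires. Section 2.4.3 has these completed online and entered directly into the database. The Figure 3 legend gives all arms the same measurements, and weight and height are measured at the centre. A reader might infer that the outcome is lifted from a form completed with the coach. No text says so, and there is no need to ask for a different source.
- **Group A is not naive.** It receives the recommendations and answers the same MeDiet questions, so it too knows which direction is favoured. That B and C see the exact cut-offs is not shown either; the article mentions grades and room for improvement, and the form itself is in a supplementary figure that is not at hand.
- **Feedback is the intervention.** Participants cannot be masked to it, and the trial calls itself a pilot.
- **Objective data exist.** Blood biomarkers and macular pigment are secondary endpoints in all arms.
- **A supporting analysis may sit in an analysis plan that is not shown.**

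The first two points stand and narrow the concern to graded, repeated feedback. The third justifies the feedback but does not make the fed-back score sufficient evidence of behaviour on its own. On the fourth, the article explores whether biomarkers reflect lifestyle change and does not use them to check the primary result. All arms also receive free antioxidants and fish oil, which may blur the nutrient markers. On the fifth, if such an analysis exists, the fix reduces to a cross-reference and a fuller limitation.

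**Conclusion.** The concern holds as a caution about interpretation that can be acted on cheaply. The primary outcome instrument is also feedback in B and coaching material in C, the trial is open label, and three of the four components are self-reported. A reporting shift of about half an SD between extreme arms would be close to the whole planning effect of 0.53 to 0.61 SD. This rests on reading 0.25 as Cohen's f and on the shift being additive.

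Three stronger readings are tempting, and the documents do not support them:
- **That reporting bias does rise from A to B to C.** The article shows only that graded contact with the form rises.
- **That over-reporting one diet item would create the whole effect.** With an assumed SD of 1.5 to 2.5 points, the target is 0.53 × 1.5 = 0.8 to 0.61 × 2.5 = 1.5 points. That SD is not in the article, and one item need not be worth one point.
- **That a positive result could never be told apart from learned answering.** Measured BMI, biomarkers and a second diet instrument are collected in all arms. What is missing is a stated role for them.

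**What to change.** In sections 3.1 and 3.3:
1. Name one key supporting analysis of the primary outcome: the same arm comparison from month 0 to month 12, with the diet part rescored from the 389-item FFQ for those items it can map. List the items it cannot map.
2. Say that this will be read alongside the arm differences in measured BMI and in the blood biomarkers.
3. State that if these do not support the form-based result, it will be reported as a change in self-reported score and not as demonstrated lifestyle change. This should be a judgement over all three sources. A rule resting on the FFQ alone would be too strict, and agreement between two self-reports could reassure falsely.

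In section 4, extend the self-report limitation from physical activity to diet and smoking, and mention that the outcome form is also an intervention tool.

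Cost: one more analysis on data already collected, and a more cautious claim. The FFQ is itself self-reported and the free supplements may mask dietary differences in the markers, so this tests for the bias without removing it.

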## 3. Study Outcomes

The study outcomes are as follows: adherence to lifestyle recommendations; identify change over time in biomarkers from blood related to AMD lifestyle determinants; the feasibility and acceptability of participants compared across the three intervention strategies, as based on quantitative and qualitative data.

### 3.1. Primary Study Outcome

Improvement of the overall lifestyle score was measured by the 13-point form (see previous paragraph and Figure S1: Lifestyle scoring form), which is based on the questionnaires inquiring about smoking habits, BMI, MeDiet, and physical activity taken at baseline and 12 months (see previous paragraph data collection and measurement).

### 3.2. Secondary Study Endpoints of AMD-Life

Improvement of the overall lifestyle score at 24 months.

Change of levels of blood biomarkers from serum/plasma and finger-prick at 12 and 24 months.

Personal feasibility and acceptability of lifestyle change measured by questionnaires at 3, 6, 9, 12, and 24 months.

Changes in macular pigment optical density as measured with MPOD at 12 and 24 months.

Changes in quantification of features (e.g., drusen) and stage of AMD as measured on multimodal images at 12 and 24 months.

#### Other Study Parameters

Other study parameters are as follows: age, gender, blood pressure, hypertension, education and socioeconomic factors, comorbidity such as cardiovascular disease, medication, genetic susceptibility of AMD evaluated by GRS, major risk and protective variants, and rare variants.

### 3.3. Statistical Analyses

To compare baseline characteristics between treatment groups we will use the Chi square test and ANOVA. We will conduct longitudinal analysis on the primary and secondary outcomes, with treatment groups as independent variables. To account for clustering within the individual due to repeated measurements, we will use mixed-effects models. We will conduct ‘intention to treat’ analysis and per protocol as a sensitivity analysis.

All statistical analyses will be carried out using R, version 3.5.3 (R Core Team, 2016) and SPSS Statistics, version 29.0.0.0 (IBM, Armonk, NY, USA).

## 4. Discussion

Achieving sustainable lifestyle change in AMD patients is challenging in daily practice. The goal of the AMD-Life study is to define the best strategy to accomplish awareness and sustainable compliance to recommendations by participants diagnosed with AMD. The study is a 1 year, three-arm (group A, B, and C), self-contained open-label randomized clinical trial, followed by an observation period in year 2.

An important strength of our study is the very detailed exploratory investigation, such as the block-wise randomized design, the close monitoring of participants, and the extensive questionnaires about the major lifestyle exposures for AMD, smoking, dietary pattern, BMI, and physical activity. We use the validated 389-dietary FFQ to measure dietary behavior and to record frequency of each intake as times per day, per week, or per month. Thereby, we are able to calculate different dietary pattern scoring methods, such as the Mediterranean diet score to achieve insight on adherence to food categories, and we are able to calculate single nutrient intake. The 16-point MeDiet screening instrument allows quick analysis of food intake and prompt determination of recommendations for change. Smoking is a well-established risk factor, but an infrequent exposure in this age-category; BMI and physical activity are less well established for AMD, but obesity and sedentary behavior are much more prevalent. An approach that combines these four exposures is likely to be more successful than a focus on only one exposure. Other strengths include extensive phenotyping of AMD features and a large set of other covariates for analysis, including biomarkers. The biomarker panel that will be assessed is very extensive, with the goal of exploring associations related to lifestyle and AMD. It involves complement factors in the active and nonactive state, oxidative stress markers, and markers of inflammation, lipids, anti-oxidants, fat soluble vitamins, minerals, and fatty acids. When confirmed, these biomarkers can serve as guidance and motivation for lifestyle change. The patient will be ‘in control’ of his/her own disease and have a better understanding of the consequences for the risks of his/her behavior.

Potential limitations of this study are the relatively small number of study participants. This study is designed as a pilot (inception phase) study. During this phase, we will set up the main elements, test our assumptions and the feasibility, check procedures, focus on adherence, and report participant and physician experience for three different strategies for stimulating a healthy lifestyle in AMD patients, specifically targeted at long-term behavioral change. Another limitation is the use of self-reported physical activity. More objective measurements could be obtained using triaxial accelerometers. A disadvantage of block randomization is that the allocation of participants could result in selection bias [56]. To reduce this bias, investigators are blinded to the randomization procedure.

Meta-analyses show that motivational interviewing (MI) is effective for decreasing alcohol and drug use in adults and adolescents, and evidence is accumulating in other areas of health, including smoking cessation, improving adherence to treatment and medication, and diabetes management [57,58,59,60]. The AMD-Life study will assess if coaching based on the behavioral change technique (BCT) [38,39] and MI [40,41] can be of additional value to change habitual behaviors and adhere to the AMD recommendations. Because implementation of a lifestyle coaching program in AMD management will be challenging, we evaluate changes in habitual behavior and assess adherence at different time points (mos. 3, 6, 9, and 12); this will provide useful information for the implementation of lifestyle coaching programs.

Over 200 clinical trials are taking place targeting various processes in the pathogenic pathway (e.g., complement activation). Aside from the direct costs, these trials also take a toll on patients, which need to be enrolled in large numbers and adhere to these trials without a warranty of benefit. It is not a secret that 90% of drug candidates in clinical trials fail, and patients who have entered trials before are usually excluded from new ones. If trials manage to be successful, new drugs rarely have the potential to reduce the risk of disease progression by half. Lifestyle intervention has this potential. AMD-Life, when validated, will provide the evidence that lifestyle changes can be achieved in persons at risk of AMD progression.

The psychological and social impact of AMD on quality of life is significant, and health-care costs related to vision loss are expected to increase exponentially over the following years [61]. Annual costs of care and treatment of AMD in Europe currently exceed €75 billion; macroeconomic costs related to visual disability can be up to €100 billion. The AMD-Life study fits well within the changing paradigm of patient and healthcare management. In general, clinical focus is moving from medical treatment of end-stage diseases to preventative actions at early stages. Insight into which strategy (A, B, or C) will stimulate preventative actions and adherence to clinical recommendations will not only slow down disease progression but also support wider clinical application of lifestyle intervention and subsequently lower patient burden and health care costs.

